#### **5.2.5. Lenalidomide Dosing and Schedule Rationale**

The current plan is to have a Safety Lead-In part of the study with lenalidomide in combination with cetuximab to establish the MTD with the combination. The starting dose of lenalidomide for the Safety Lead-In part is proposed to be 25 mg daily due to the clinical data with lenalidomide in other indications. Currently lenalidomide is approved as a treatment for MDS at a dose of 10 mg daily and for treatment of MM at a dose of 25 mg once each day for days 1-21 of a 28 day cycle. While myelosuppression is the major dose-limiting toxicity in patients with hematologic disorders who are taking lenalidomide treatment, evidence exists that lenalidomide tolerability may be improved for patients without hematological malignancies or compromised bone marrow. For example, in a dose escalation study entitled, "Phase I study of lenalidomide, a novel thalidomide analog, in patients with refractory metastatic cancer," Tohny et al enrolled 45 patients with refractory, metastatic solid tumors. Patients were enrolled to receive single agent lenalidomide 5 to 40 mg administered on days 1-21 of each 28-day treatment cycle.

Lenalidomide was well-tolerated up to 35 mg. Within the study, the following grade 3 toxicities were seen: diarrhea (1), hypotension (1), pulmonary effusions (1), and thrombosis (2). Grade 4 adverse events included 2 patients with neutropenia, one patient with arrhythmia, and a single patient with hemolysis ([Tohny, 2006](#)). It was suggested that lenalidomide may have a lower incidence and severity of myelosuppression in solid tumors compared to myelosuppression observed in patients with hematologic malignancies or compromised bone marrow.

Lenalidomide studies performed in prostate cancer patients have found that both as single agent and in combination with other agents including docetaxel, lenalidomide is well-tolerated at doses of at least 25 mg or higher in some cases ([Petrylak, 2009](#); [Sanborn, 2008](#)).

Lenalidomide is proposed to be administered continuously on Days 1-28 of each 28-day cycle to potentially maximize the combined ADCC effects of the two drug combination.

The Phase 2b – Proof of Concept (POC) will use the combination dose established from the Safety Lead-In part and lenalidomide 25 mg as a single agent dose. The Phase 2b – Expansion part will use the combination dose established from the Safety Lead-In part.

#### **5.2.6. Study Rationale**

Colorectal cancer therapy has developed extensively over the last 10 years. Patients were initially being treated with single agent 5-FU only, and now they have access to multiple lines of therapy which significantly increased overall survival through the introduction of 5-FU based chemotherapeutic regimens plus the introduction of novel treatment modalities such as anti-angiogenesis and EGFR inhibition.

Even though an increase in overall survival has been achieved through the use of these novel therapies, there is still a high unmet clinical need in patients that progress through the different lines of therapy and become resistant to the available drugs. The recent understanding of the impact of gene point mutations affecting the EGFR signaling pathways helped to define

subgroups of patient populations that lack proven treatment alternatives. One such population consists of patients that harbor point mutations on the KRAS gene which results in the constitutive activation of the EGFR signaling pathway driving the cell into mitosis.

Lenalidomide has the potential for clinical activity in solid tumors due to a variety of mechanistic properties that may lead to cancer growth inhibition including, immune modulation, anti-angiogenesis and effects within the tumor microenvironment. Evidence that lenalidomide is a potent immunomodulator with anti-angiogenic activity provides the non-clinical rationale for evaluating lenalidomide in colorectal cancer. Based on preclinical and in vitro studies highlighted above, Celgene Corporation expects that lenalidomide in combination with cetuximab will enhance T cell and NK cell activation leading to enhanced NK cell-mediated ADCC of colorectal tumor cells, regardless of KRAS mutational status and subsequent clinical benefit for CRC patients.

## **6. STUDY OBJECTIVES**

### **6.1. Primary**

#### **6.1.1. Phase 2a**

- To determine the Maximal Tolerated Dose (MTD) of lenalidomide in combination with cetuximab in subjects with KRAS mutant metastatic CRC.

#### **6.1.2. Phase 2b**

- To determine the response rate in subjects with KRAS mutant metastatic CRC.

### **6.2. Secondary (all phases)**

- To evaluate the safety and tolerability in subjects with KRAS mutant metastatic CRC.
- To assess the clinical efficacy in subjects with KRAS mutant metastatic CRC.

### **6.3. Exploratory (all phases)**

- Analysis of biomarkers as measures for validation of clinical efficacy and toxicity.

## **7. STUDY ENDPOINTS**

### **7.1. Primary**

#### **7.1.1. Phase 2a**

- Maximum Tolerated Dose

#### **7.1.2. Phase 2b**

- Response Rate according to Response Evaluation Criteria in Solid Tumors 1.1 (RECIST 1.1) ([Eisenhauer, 2009](#)).

### **7.2. Secondary**

- Progression Free Survival.
- Safety / Tolerability (type, frequency, severity, and relationship of adverse events to investigational products).
- Duration of Response.
- Disease Control Rate.
- Overall Survival.

### **7.3. Exploratory**

- Assessment of biomarkers including, but not limited to:
  - Immuno flow cytometry panel for T cells and NK cells.
  - Cytokines/immune markers.
  - Growth factors.
  - Circulating tumor cells.
  - FCgR polymorphisms.
  - EGFR copy number.

## 8. OVERALL STUDY DESIGN

This is a Phase 2, multicenter, open-label study of lenalidomide in combination with cetuximab in subjects with KRAS mutant metastatic CRC. The primary objective of the study is to determine the MTD in Phase 2a and response rate in Phase 2b. The secondary objectives are to evaluate the safety, tolerability, and efficacy.

Subjects will be screened within 28 days of study entry as outlined in [Table 2](#). Up to approximately 220 subjects meeting all eligibility criteria will be enrolled into this 3-part study. Each of the three parts of this study; Phase 2a - Safety Lead-In, Phase 2b - POC, and Phase 2b - Expansion, are described below. Laboratory testing will be performed by a central laboratory for this study.

Subjects will continue on study treatment until documented disease progression per RECIST 1.1, unacceptable toxicity, death, or treatment discontinuation for any other reason. Subjects should be provided with appropriate supportive care throughout the study.

### 8.1. Phase 2a – Safety Lead-In

Approximately 6-18 subjects meeting all eligibility criteria will be enrolled by IVRS into the Phase 2a – Safety Lead-In part receiving treatment with lenalidomide in combination with cetuximab to establish the MTD with the combination.

#### 8.1.1. Safety Lead-In Dose Finding

Initially 6 subjects will be enrolled and treated with a daily oral dose of lenalidomide at 25 mg administered on Days 1-28 of each 28-day cycle and intravenous (IV) infusions of cetuximab (400 mg/m^2 first infusion only, then 250 mg/m^2 subsequently) administered on Days 1, 8, 15, and 22 of each 28-day cycle.

- If < 2 of the 6 subjects experience a Dose Limiting Toxicity (DLT), then the Phase 2b – POC part will start with lenalidomide at 25 mg.
- If  $\geq 2$  of the 6 subjects experience a DLT, then 6 additional subjects will be enrolled at lenalidomide 20 mg.
  - If < 2 of the additional 6 subjects experience a DLT, then the Phase 2b – POC part will start with lenalidomide at 20 mg.
  - If  $\geq 2$  of the additional 6 subjects experience a DLT, then 6 additional subjects will be enrolled at lenalidomide 15 mg.
    - If < 2 of the additional 6 subjects experience a DLT, then the Phase 2b – POC part will start with lenalidomide at 15 mg
    - If  $\geq 2$  of the additional 6 subjects experience a DLT, then Celgene Corporation will discuss with the investigators and reassess the doses.

Dosing does not escalate during the safety lead-in part of the study. In addition, there will be no intra-patient dose escalation. Cycles will be repeated every 28 days. All subjects will continue on

investigational product(s) until documented tumor progression, unacceptable toxicity, death, or treatment discontinuation for any other reason.

### **8.1.2. Safety Lead-In Definition of Dose Limiting Toxicity**

DLT is defined as one or more of the following:

- Total of  $\geq 7$  days of lenalidomide and/or  $\geq 1$  dose of cetuximab missed during the first cycle due to drug-related toxicity as outlined below:
  - Any Grade 3 or 4 non-hematological toxicity (excluding alopecia), even after optimally treated with supportive measures.
    - A rash with suspected relationship to cetuximab, treated and resolved in accordance with the guidelines will not be considered a DLT.
  - Grade 4 neutropenia or febrile neutropenia.
  - Grade 4 thrombocytopenia.

Should any subject discontinue the study prior to completing the entire first cycle for reasons other than a DLT or if  $\geq 7$  days of lenalidomide and/or  $\geq 1$  dose of cetuximab were missed during the first cycle for reasons other than a DLT, then a replacement subject will be added at that dose level.

The occurrence of one of the above drug-related toxicities will result in a clinical and/or laboratory assessment to be performed within 7 days following the initial finding to examine the subject for resolution of the toxicity. Lack of resolution of any of these toxicities according to the guidelines above or within 7 days of scheduled start of Cycle 2 Day 1 will be considered a DLT. Subjects who experience a DLT may continue on treatment at the Investigator's discretion at a lower dose of lenalidomide in accordance with [Table 6](#).

Adverse events will be graded using the CTCAE Version 4.0 ([http://ctep.cancer.gov/protocolDevelopment/electronic\\_applications/docs/ctcae4.pdf](http://ctep.cancer.gov/protocolDevelopment/electronic_applications/docs/ctcae4.pdf)).

If cetuximab is discontinued, lenalidomide may be continued until documented tumor progression, unacceptable toxicity, death, or treatment discontinuation for any other reason.

Following Cycle 1, all subjects will continue on assigned treatment until documented tumor progression, unacceptable toxicity, death, or treatment discontinuation for any other reason and be followed for toxicity and secondary endpoints.

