### **8.1.3. Safety Lead-In Definition of MTD**

The MTD of lenalidomide will be defined as the highest dose level at which no more than 1 out of 6 subjects experience a DLT during Cycle 1 of lenalidomide in combination with cetuximab.

Safety measurements and analysis will be performed at each visit as outlined in [Table 2](#).

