### **10.3. Dose Modification or Interruption**

Dose modifications of lenalidomide and cetuximab are not permitted during Cycle 1 of the Phase 2a – Safety Lead-In part, unless a subject experiences a DLT, however permitted anytime after Cycle 1 during Phase 2a – Safety Lead-In, anytime during Phase 2b –POC and Phase 2b – Expansion.

For toxicities consistent with cetuximab administration, discontinuation, dose interruptions and/or reductions see Section 10.3.2 and the approved product labeling. If toxicities are believed to be attributed to lenalidomide administration, please see Table 6 for dose modification guidelines. Doses of any investigational product cannot be re-escalated once reduced. Any investigational product (lenalidomide and/or cetuximab) held > 14 days must be discontinued. If cetuximab is discontinued per protocol and for reasons other than disease progression, lenalidomide may be continued until documented tumor progression, unacceptable toxicity, death, or treatment discontinuation for any other reason.

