### 10.3.1. Lenalidomide Dose Modification or Interruption

**Table 6: Dose Modification Guidelines for Lenalidomide**

| Toxicity                                                            | Grade | Dose Modification                                                                                                                                                                                                                                                                                    |
|---------------------------------------------------------------------|-------|------------------------------------------------------------------------------------------------------------------------------------------------------------------------------------------------------------------------------------------------------------------------------------------------------|
| Rash                                                                | 3     | Hold lenalidomide until resolution to $\leq$ Grade 2; at first occurrence resume at same dose of lenalidomide; at second occurrence resume lenalidomide at 5 mg reduction in dose. Further dose reductions are permitted to a minimum of 5 mg.
If rash is desquamating, discontinue lenalidomide. |
|                                                                     | 4     | Discontinue lenalidomide.                                                                                                                                                                                                                                                                            |
| Sinus bradycardia, atrial fibrillation or other cardiac arrhythmias | 2     | Hold lenalidomide until resolution to $\leq$ Grade 1, resume lenalidomide at 5 mg reduction in dose. Additional dose reductions are permitted to a minimum of 5 mg.                                                                                                                                  |
|                                                                     | 3 / 4 | Discontinue lenalidomide.                                                                                                                                                                                                                                                                            |

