| Other non-hematological toxicity assessed as lenalidomide-related   | 3 / 4 | Hold until resolution to $\leq$ Grade 2; resume lenalidomide at 5 mg reduction in dose. Additional dose reductions are permitted to a minimum of 5 mg.                                                                                                                                               |

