#### 10.3.2.2. Skin Toxicity

If a subject experiences Grade 3 skin toxicity, cetuximab therapy may be delayed for up to 14 days without changing the dose level (see [Figure 3](#)). The investigator should also consider concomitant treatment with topical and oral antibiotics; topical corticosteroids are not

recommended. If the toxicity resolves to Grade 2 or less by the following treatment period, treatment may be resumed. If Grade 3 skin toxicity occurs for a second and third time, cetuximab therapy may again be delayed for up to 14 days with concomitant dose reductions to 200 mg/m^2 and then 150 mg/m^2. Cetuximab dose reductions are permanent. Subjects must discontinue cetuximab if more than 2 consecutive infusions are withheld or Grade 3 skin toxicity occurs for a fourth time despite appropriate dose reduction.

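### The DLT rash exemption ignores what happens to lenalidomide, so a resolved rash suspected of both drugs can meet a Table 6 stopping criterion and not count towards the lenalidomide MTD

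*Protocol*

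**What the plan says.** Section 8.1.2 of the Protocol makes a toxicity a DLT only if it costs dosing in Cycle 1: at least 7 days of lenalidomide, or at least one "dose of cetuximab missed during the first cycle due to drug-related toxicity as outlined below". The list that follows includes Grade 3 or 4 non-hematological toxicity, and directly under that item stands the exemption: "A rash with suspected relationship to cetuximab, treated and resolved in accordance with the guidelines will not be considered a DLT". The synopsis repeats it. The guidelines are not identified by section.

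Three other rules bear on the same rash.

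- **Dose modification (Section 10.3).** Toxicity consistent with cetuximab goes to Section 10.3.2 and the product labeling. For lenalidomide, "If toxicities are believed to be attributed to lenalidomide administration, please see Table 6 for dose modification guidelines". The same section does not allow either drug's dose to be modified in Cycle 1 of Phase 2a unless the subject has a DLT, and it requires any product held for more than 14 days to be discontinued.
- **Table 6, rash.** At Grade 3, lenalidomide is held and later resumed, but "If rash is desquamating, discontinue lenalidomide". At Grade 4 it is discontinued.
- **Section 10.3.2.2, cetuximab skin toxicity.** The text deals with Grade 3: "If the toxicity resolves to Grade 2 or less by the following treatment period, treatment may be resumed".

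On replacement, Section 8.1.2 says that if at least 7 lenalidomide days or at least one "dose of cetuximab were missed during the first cycle for reasons other than a DLT, then a replacement subject will be added" to the same level. Section 8.1.3 defines the MTD as the "highest dose level at which no more than 1 out of 6 subjects experience a DLT during Cycle 1" of the combination.

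**The concern.** The lead-in exists to choose the lenalidomide dose. Table 5 gives one cetuximab regimen for all three levels, and only lenalidomide changes (25, 20, 15 mg). Exempting a manageable cetuximab rash from that decision is sensible. The difficulty is that the exemption turns only on a suspected link to cetuximab and on resolution. It does not ask whether lenalidomide is suspected too, or whether the rash was bad enough that lenalidomide had to stop.

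This reverses the expected order of severity. Any other lenalidomide-related Grade 3 non-hematological toxicity that costs 7 or more lenalidomide days is a DLT, although Table 6 lets that subject "resume lenalidomide at 5 mg reduction in dose. Additional dose reductions are permitted to a minimum of 5 mg". A desquamating Grade 3 rash suspected of both drugs, for which Table 6 allows no resumption, escapes the count once it resolves.

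The decision turns on one versus two DLTs in six subjects, so one event classified the wrong way can decide whether a level goes forward to the combination arm of the proof-of-concept part (up to 41 subjects) and possibly to the Expansion (about 120).

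**Working it through.** **Following one rash through the text.** Take a desquamating Grade 3 rash in Cycle 1 that the investigator suspects of both drugs.

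1. Appendix 21.2 asks for causality as suspected or not suspected for the investigational product(s). It does not rule out suspecting both, and both drugs start on Day 1.
2. Because lenalidomide is suspected, Section 10.3 points to Table 6, which says to discontinue it.
3. The missed-dose threshold is met if lenalidomide stops by Day 22 (Days 22 to 28 are 7 days) or if a cetuximab dose is missed.
4. The rash falls to Grade 2 or less, which is the level Section 10.3.2.2 uses for resuming cetuximab. The backstop in Section 8.1.2 makes only lack of resolution a DLT, so it does not apply.
5. The exemption applies and the rash is not a DLT. Dosing was therefore missed for a reason other than a DLT, and a replacement subject is added.
6. Section 10.3 bars the modification made in step 2 because no DLT occurred. The site holds two instructions that cannot both be followed.

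**Size.** The protocol states no operating characteristics for the lead-in, so there is no figure to reproduce, and it gives no rash or DLT rates. Every rate below is an assumption. Let *p* be the probability of another DLT and *r* the probability of an exempted rash of this kind. A level passes with at most 1 DLT in 6, where P(Bin(6, x) ≤ 1) = (1 − x)^6 + 6x(1 − x)^5.

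- As written, subject replaced: x = p/(1 − r)
- Subject kept as a non-DLT: x = p
- Rash counted as a DLT: x = p + r

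Example with p = 0.15 and r = 0.02. As written, x = 0.15/0.98 = 0.153 and the pass probability is 0.769. Counted, x = 0.17 and it is 0.729. The gap is about 4 points.

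| p | r | As written | Counted | Gap (points) |
|---|---|---|---|---|
| 0.10 | 0.01 | 0.884 | 0.866 | 1.8 |
| 0.10 | 0.02 | 0.882 | 0.844 | 3.7 |
| 0.10 | 0.05 | 0.875 | 0.776 | 9.9 |
| 0.15 | 0.01 | 0.773 | 0.753 | 2.0 |
| 0.15 | 0.02 | 0.769 | 0.729 | 4.1 |
| 0.15 | 0.05 | 0.758 | 0.655 | 10.2 |
| 0.20 | 0.01 | 0.650 | 0.631 | 2.0 |
| 0.20 | 0.02 | 0.645 | 0.606 | 3.9 |
| 0.20 | 0.05 | 0.630 | 0.534 | 9.6 |

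Gaps were taken before rounding. Across these rows the gap is 1.8 to 2.0 times *r*. At p = 0.15 and r = 0.001 it is 0.2 points. With fewer other DLTs the multiple is smaller: at p = 0.05 and r = 0.02 the probabilities are 0.966 and 0.939, a gap of 2.7 points, or about 1.3 times *r*.

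Keeping the subject as a non-DLT would give 0.886, 0.776 and 0.655 at p = 0.10, 0.15 and 0.20, slightly above the as-written column. The gap therefore comes from the exemption and not from replacement, which is marginally stricter than keeping the subject.

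The chance of at least one such rash among six subjects is 1 − (1 − r)^6: 6%, 11% and 26% for r = 1%, 2% and 5%.

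**The case against.** **Section 10.3 blocks the path.** It forbids dose modification in Cycle 1 of the lead-in unless a DLT occurs, and Table 6 lists discontinuation in its dose modification column. On that view, stopping lenalidomide presupposes a DLT. The sentence does matter, because it means nobody can assume that lenalidomide was in fact stopped. But it does not make an expressly exempted rash a DLT. It leaves Table 6 requiring a stop that Section 10.3 disallows, so the fix should depend on meeting the stopping criterion and not on the stop having happened.

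**Toxicity is routed by attribution.** The exemption may have been meant for rash managed purely as cetuximab toxicity, and the definition of a suspected relationship asks that other medications not be a sufficient explanation. This makes dual suspicion less common. It does not bar it, and the exemption does not say that lenalidomide must be unsuspected.

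**Grade 4.** Because no grade limit is written, a reader might infer that any Grade 4 rash is plainly exempt. The documents do not establish that. If the guidelines are those of Section 10.3.2.2, its text covers only Grade 3. Figure 3 is not reproduced in the copy reviewed, and Section 10.3 also invokes product labeling that is not at hand. The firm case is the desquamating Grade 3 rash.

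**Rarity.** The event needs suspicion of both drugs, a stopping criterion, enough missed dosing and timely resolution; Section 8.1.2 requires a check within 7 days and counts lack of resolution as a DLT. This stands. The joint event is probably uncommon, and the assumed 1% to 5% has no support in the protocol.

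**Conclusion.** The point holds in a limited form. As written, a rash suspected of both drugs that meets a Table 6 criterion for stopping lenalidomide, costs enough Cycle 1 dosing and then resolves is not a DLT, and the subject is replaced. This is clear for a desquamating Grade 3 rash and arguable for Grade 4. Sections 8.1.2 and 10.3 and Table 6 also give the site conflicting instructions for that subject.

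For other-DLT rates between 10% and 20%, the change in the chance that a level passes is about twice whatever rate is assumed for such rashes. A reader might infer that the MTD will be materially too high, or that 10 points is the expected effect. Neither follows: 10 points simply reflects an assumed rate of 5%, and the protocol gives nothing from which to choose a rate. Nor does the replacement rule raise the pass rate. The case for changing the wording is that the lead-in sets the lenalidomide dose and the correction is cheap.

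**What to change.** Change the exemption in Section 8.1.2 and in the synopsis.

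1. Define resolved as resolved to Grade 2 or less, and replace the unspecified reference to guidelines with Section 10.3.2.2.
2. Append this clause: *unless it is also suspected to be related to lenalidomide and meets a Table 6 criterion for lenalidomide discontinuation (Grade 4, or desquamating Grade 3) or leads to lenalidomide being held > 14 days and discontinued; such a rash is a DLT.*

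Tying the clause to the criterion removes the conflict with Section 10.3 for these rashes: the rash is a DLT, so the Cycle 1 stop is allowed. The second limb covers a non-desquamating rash that ends lenalidomide through the 14-day rule. The replacement sentence can stay as it is, and ordinary cetuximab rash remains exempt.

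The cost is one clause and one cross-reference in two places, with no added visits. The downside is that a dose level may fail slightly more often, by the gaps in the table if those rates applied.

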### **10.6. Discontinuation from Treatment**

The following events are considered sufficient reasons for discontinuing a subject from investigational product(s):

- Adverse event(s) (AEs) that, in the judgment of the Investigator, may cause severe or permanent harm or which rule out continuation of investigational product(s).
- Disease progression
- Subject withdraws consent
- Subject lost to follow-up
- Death
- Protocol violation

The reason for discontinuation should be recorded in the CRF and in the subject's medical records. An IVRS call is required when discontinuing any investigational product.

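### The lead-in DLT definition names no Grade 5 event, so a drug-related Cycle 1 death with no listed toxicity before it is replaced rather than counted in the 1-of-6 MTD rule

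*Protocol*

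**What the plan says.** Section 8.1.2 and the synopsis give the same DLT list. A DLT requires at least 7 missed days of lenalidomide and/or at least one "dose of cetuximab missed during the first cycle due to drug-related toxicity as outlined below". The qualifying toxicities are "Any Grade 3 or 4 non-hematological toxicity (excluding alopecia), even after optimally treated with supportive measures", Grade 4 neutropenia or febrile neutropenia, and Grade 4 thrombocytopenia. A further sentence makes a listed toxicity that fails to resolve a DLT.

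The replacement sentence opens "Should any subject discontinue the study prior to completing the entire first cycle for reasons other than a DLT". It also covers subjects who miss the same amount of dosing for some cause that is not a DLT. In both cases a new subject is added at that dose level. Drug-related exits are not treated separately.

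The count drives the dose directly. Section 8.1.3 defines the MTD as the highest dose at which "no more than 1 out of 6 subjects experience a DLT during Cycle 1". Under Section 8.1.1, fewer than two DLTs at 25 mg starts the POC part at 25 mg; when two or more "of the 6 subjects experience a DLT, then 6 additional subjects will be enrolled at lenalidomide 20 mg".

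Elsewhere the protocol does treat death as its own category. The severity scale in Section 21.2, for events that CTCAE does not define, separates Grade 4 (life threatening) from Grade 5 (death). Section 10.6 lists death among the reasons for discontinuation.

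**The concern.** A death suspected to be caused by the study drugs is the most serious toxicity a lead-in can show, and the rule should count it. The list as worded does not clearly do so. Because replacement is tied to that list and not to whether the drugs caused the exit, a subject whose drug-related death fits no listed item is handled like one who leaves for an unrelated reason.

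The MTD is the Phase 2a primary endpoint. The dose it clears goes to Arm 1 of the POC part (up to 41 subjects) and, if that arm is positive, to the Expansion (about 120). Section 8.1.1 states no override at 25 mg or 20 mg; discussion between sponsor and investigators is named only after 15 mg fails.

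**Working it through.** The protocol gives no operating characteristic for the lead-in, so there is no figure to reproduce.

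**1. Does a drug-related death with no listed toxicity before it meet any DLT clause?** Take a sudden death recorded directly as Grade 5.
- Non-hematological item: Grade 3 or 4 only, so not met.
- Neutropenia, febrile neutropenia and thrombocytopenia items: not met.
- Failure-to-resolve clause: it applies only to toxicities already on the list, so not met.
- Replacement sentence: the subject has left during Cycle 1 and no DLT clause applies, so the subject is replaced.

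**2. Missed-dose threshold.** If the last lenalidomide dose is on Day d, the lenalidomide days missed are 28 − d, and the cetuximab doses missed are those of Days 1, 8, 15 and 22 that fall after d.
- d = 21: 28 − 21 = 7 days and one cetuximab dose (Day 22) missed. Threshold met.
- d = 22: 28 − 22 = 6 days and no cetuximab dose missed. Threshold not met, and likewise for d = 23 to 28.

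A death late in the cycle therefore fails the threshold as well as the grade list. Adding Grade 5 to the list alone would not capture it.

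**3. Worked case at 25 mg: six subjects, one listed DLT, one such death.**
- Death counted: 2 of 6, so the next cohort is at 20 mg.
- As written: the death is replaced, and 25 mg is cleared if the replacement has no DLT. With listed-DLT probability p, that has probability 1 − p: 0.90, 0.85, 0.80 and 0.75 for assumed p of 0.10, 0.15, 0.20 and 0.25.

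**4. Overall effect.** Let q be the per-subject probability of such a death. Both p and q are assumptions. A dose is cleared with probability P(X ≤ 1) = (1 − π)^6 + 6π(1 − π)^5, where π = p/(1 − q) as written (deaths replaced) and π = p + q if deaths count. For p = 0.15 and q = 0.01:
- As written: π = 0.15/0.99 = 0.1515, giving 0.773.
- Counted: π = 0.16, giving 0.753.

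| p | q = 0.01, as written / counted | q = 0.02, as written / counted | q = 0.05, as written / counted |
|---|---|---|---|
| 0.10 | 0.884 / 0.866 | 0.882 / 0.844 | 0.875 / 0.776 |
| 0.15 | 0.773 / 0.753 | 0.769 / 0.729 | 0.758 / 0.655 |
| 0.20 | 0.650 / 0.631 | 0.645 / 0.606 | 0.630 / 0.534 |

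The gap is about 0.02, 0.04 and 0.10. The last column is an upper illustration: 5% is a high rate for deaths that pass through no listed toxicity.

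**5. How often does the worked case arise?** One listed DLT and one such death among the first six has probability 30·p·q·(1 − p − q)^4. At p = 0.15:
- q = 0.01: 30 × 0.15 × 0.01 × 0.84^4 = 0.022.
- q = 0.02: 30 × 0.15 × 0.02 × 0.83^4 = 0.043.

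**6. Is replacement itself the cause?** Keeping these subjects in the six as non-DLTs gives π = p, which is 0.776 at p = 0.15. With replacement the figures are 0.773, 0.769 and 0.758. Replacement is slightly stricter, so the cause is the incomplete list.

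**The case against.** The strongest reply is that no sensible team would exclude a drug-related death. Most fatal toxicities pass through Grade 3 or 4, febrile neutropenia or a Grade 4 cytopenia, and a listed toxicity that ends in death has plainly not resolved. That stands and confines the gap to deaths with no listed toxicity before them. It does not close the gap, because the remaining case depends on staff departing from the text.

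Other controls exist. Serious adverse events reach the sponsor within 24 hours (Section 21.2), the sponsor may terminate the study (Section 19.2), replaced subjects remain in the Safety Population (Section 15.1), and doses may be modified in Phase 2b (Section 10.3). These reduce harm, but none of them corrects the DLT count.

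A reader might infer three stronger points that the protocol does not support:
- **That permanent stops for lower-grade drug toxicity must also count.** Section 10.6 lets a subject stop for events that "in the judgment of the Investigator, may cause severe or permanent harm or which rule out continuation of investigational product(s". Any DLT definition needs a grade threshold, and leaving such stops below it is a choice for the clinical team, not an error. The entries in Table 6 that require immediate discontinuation of lenalidomide are already Grade 3 or 4 non-hematological events.
- **That replacement biases the MTD.** Step 6 of the working shows that it does not.
- **That 25 mg is likely to be cleared after several deaths.** With two such deaths, no listed DLT and both replaced, 25 mg is cleared with probability 0.98 at p = 0.15. But that starting event has probability 15·q²·(1 − p − q)^4, about 0.0007 at q = 0.01 and 0.003 at q = 0.02.

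**Conclusion.** The point holds in a narrow form. As written, a Cycle 1 death suspected to be drug-related, with no listed toxicity before it, falls outside the DLT definition and is replaced. The rule can then clear a dose at 1 of 6 when the count should be 2 of 6. That follows from the text without any assumed rate.

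The overall size does not. Under assumed listed-DLT rates of 10% to 20%, the probability of clearing a dose is too high by about 0.02 if such deaths occur in 1% of subjects and about 0.04 if in 2%. The protocol gives no rate for either. The change is still worth making, because it concerns patient safety and the Phase 2a primary endpoint and needs very little text.

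**What to change.** In Section 8.1.2 and the synopsis, add to the DLT definition any Cycle 1 death (Grade 5 event) suspected to be related to lenalidomide or cetuximab, regardless of the number of doses missed. The causality category is the one already defined in Section 21.2. In the replacement sentence, state that such subjects are not replaced. The missed-dose waiver is needed because of deaths after a last dose on Days 22 to 28.

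The cost is one phrase and one clause in two places. A dose level may fail slightly more often, which could add six subjects at 20 mg or 15 mg. That stays within the planned maximum of about 18 (three levels of six). Whether lower-grade permanent discontinuations should also count can be left to the clinical team.
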